### Study procedures

The study design is presented in Figure 1.

**Figure 1 F1:**
[figure not shown]
**Overview of study procedures**.

In the Dutch social security system, workers that are long term sick-listed can apply for a disability benefit at approximately 91 weeks after the start of their sick leave. Around the 102^nd ^week of being sick-listed, these workers will receive an invitation from UWV to visit an insurance physician,. Together with this standard invitation from UWV, this study will send along an invitational letter and the study's information brochure. In this brochure, instructions are given on how to participate in the study by filling out an online application form. This online form includes questions concerning the study's in- and exclusion criteria and an informed consent. Subjects who meet all the criteria and are willing to participate in the research will be directed to the baseline questionnaire (T_0_). When subjects finish filling out the baseline questionnaire, they will be randomized in either the intervention group or control group. Disability claimants who are randomized into the intervention group, will receive an email with a username and password that gives them full access to the website intervention. Participants who are randomized into the control group receive an email that directs them to a website with commonly available information only. Before each follow-up measurement, subjects from both groups will receive emails in which they are asked to fill out the online questionnaires. Reminders will be sent to increase compliance.

Insurance physicians receive a newsletter with information about the ongoing of the project. Directly after a disability assessment with a claimant participating in the study, insurance physicians will be asked to fill out a short questionnaire, which they will receive by email.

#### Outcomes

Measurements will take place on five different occasions:

- T_0_: Baseline measurement. Approximately 2 weeks before the disability assessment.

Questionnaire filled out by claimants.

- T_1_: Two days before the disability assessment.

Questionnaire filled out by claimants.

- T_2_: Directly after finishing the disability assessment.

Questionnaires filled out by claimants and insurance physicians.

- T_3_: Six weeks after the disability assessment. At this point, claimants will be informed on the decision about their disability pension.

Questionnaire filled out by claimants.

- T_4_: Four months after the disability assessment, a follow-up measurement will take place.

Questionnaire filled out by claimants.

All outcomes will be measured through online questionnaires [see Additional file 2]:

### Primary outcome

#### Empowerment

The main outcome measure will be empowerment. Because of the absence of a generally accepted measurement scale for this variable, the so-called "VrijBaan questionnaire" was developed: an instrument that has been designed to measure empowerment among people with a work disability [43]. The VrijBaan questionnaire consists of 60 items divided over six subscales (Competence:13 items, Self-determination:11 items, Meaning:9 items, Impact:8 items, Positive Identity:10 items, Group Orientation:9 items). Each subscale contains components of previously validated instruments that measure specific components of empowerment (such as the General Self-efficacy scale [46] or the Pearlin Mastery Scale [47]).

Internal consistency of the VrijBaan questionnaire was found to be good. After testing the questionnaire in a representative population (n = 385) all subscales showed Cronbach's alphas higher than 0.80 [43].

Due to the length of the questionnaire we choose to only include the subscales Impact and Competence in the T_1 _measurement. Furthermore, in order to make international comparisons with other empowerment-related studies we added five questions of the General Self-efficacy scale and two questions of the Pearlin Mastery Scale that were not included in the Vrijbaan questionnaire. The constructs measured with these scales (self-efficacy and mastery respectively) are often associated with empowerment.

Finally, we added two adapted questions from the Pearlin Mastery Scale in order to measure context specific empowerment.

### Secondary outcomes

#### Claimants satisfaction

The satisfaction of claimants with their insurance physicians will be measured with the AStri questionnaire [48]. This questionnaire, which is specially designed to measure patient satisfaction in the field of insurance medicine, contains 29 items divided over six subscales, each representing a different component of patient-insurance physician interaction (Listening, Empathizing, Correctness, Clearness, Rigorousness, and Professionalism). Testing of this questionnaire resulted in a good internal consistency (all subscales had a Cronbach's alpha greater than 0.78) [48].

#### Physicians satisfaction

Insurance physicians satisfaction with the disability assessment and claimants attitude will be assessed with a questionnaire specially designed for this study. In this 10-item questionnaire physicians can answer questions on a 5-point Likert scale ranging from *I totally disagree *to *I totally agree*. In addition, physicians will be asked how actively claimants were participating during the assessment and how much time they spent on the assessment.

#### Claimants perceived justice

To measure claimants feelings of justice with the final verdict on their disability pension, a Dutch translation of Moorman's [49] justice questionnaire will be used [50]. This questionnaire consists of 30 items measuring three dimensions of justice perceptions: distributive justice (the perception of fairness of the outcomes a claimant receives; 7 items), procedural justice (the perception of fairness of the procedures used to determine these outcomes, 12 items), and interactional justice (the perception of fairness of contact with the organization that determines the outcomes, 11 items). Each item can be scored on a 7-point scale ranging from "*I totally do not agree*" (1 point) to "*I totally agree*" (7 points). Average scores are calculated for each separate dimension. In the present study we will only use the subscales distributive justice and procedural justice. Cronbach's alpha for these dimension of the questionnaire was proven to be high (distributive justice: α = 0.91, procedural justice: α = 0.82) [51].

#### Subjective knowledge

With a 10-point Visual Analogue Scale (VAS), we will measure claimants subjective knowledge about social security law arrangements and disability assessment procedures. At T_0 _we will ask: "How much do you know about social security law arrangements and disability assessment procedures?" (1 = I know nothing, 10 = I know everything). At T_1 _we will ask: "To what extent did the intervention increase your knowledge about social security law arrangements and disability assessment procedures?" (1 = my knowledge did not increase, 10 = I gained maximum knowledge).

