### Process evaluation

Among the participants of the intervention group, experiences with the use of the intervention will be evaluated. This evaluation will be assessed with a brief questionnaire at T_3_. This questionnaire contains both quantitative (e.g. a generic grade for the website) and qualitative questions (e.g. "Do you have any suggestions to improve the website?"). Reasons for complying or not complying will be asked in this questionnaire as well, in order to obtain insight into the potential success of implementation.

Furthermore, the website http://www.wiagesprek.nl will automatically collect data on website usage, so that we can determine compliance and which components are most frequently used. All actions on the website of each claimant will be tracked and stored in a database.

After finishing the research, we will interview five claimants and five insurance physicians, who assessed disability of study participants, on their experiences with the intervention.

For an overview of measurements, see table 1.

**Table 1 T1:** Schedule of measurements

Outcome measure	T_0_: 2 weeks prior to disability assessment	T_1_: Prior to disability assessment	T_2_: After disability assessment	T_3_: 6 weeks after disability assessment	T_4_: 4 months after disability assessment
*Empowerment**	X	X			X

*Claimants satisfaction*			X		

*Perceived Justice*				X	

*Subjective knowledge*	X	X			

*Claimants expectations*	X	X	X		

*Coping Strategy*	X	X			

*Perceived Work Ability*	X	X			X

*Claimants preparation*		X			

*Return to Work*					X

*Process Evaluation*				X	

*Physicians satisfaction*			X		

* The following subscales from the VrijBaan empowerment questionnaire are included in the questionnaire:

T_0_: all subscales

T_1_: subscale Competence and Impact

T_4_: all subscales

NB: The Pearlin Mastery Scale and the General Self-efficacy scale can be distracted from the T_0_, T_1 _and T_4 _measurement

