### Statistical analysis

Baseline values will be analyzed for differences between the two groups, by one-way-analysis of variance for numerical data and chi-square for categorical data. The primary analysis will be a comparison of the change in empowerment between the intervention and control group following the "intention-to-treat" principle. On data from questionnaires filled out on more than one occasion (e.g. empowerment, coping strategy, knowledge) we will use a repeated measurement analysis to test if both research groups diverged from baseline to follow-up. With data that will be measured on one occasion (e.g. claimant satisfaction, insurance physicians satisfaction and perceived justice) we will use t-tests to detect possible differences between the two research groups. Additionally, a per-protocol analysis will be performed.

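### Subjective knowledge is rated as a level at T0 and as a perceived gain at T1, so the planned repeated-measures test of it does not measure change in knowledge

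*Protocol article*

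**What the plan says.** The protocol article, under Secondary outcomes, Subjective knowledge, uses one 10-point scale with two different questions.

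- **T0:** "How much do you know about social security law arrangements and disability assessment procedures", with anchors "1 = I know nothing, 10 = I know everything".
- **T1:** "To what extent did the intervention increase your knowledge about social security law arrangements and disability assessment procedures", with anchors "1 = my knowledge did not increase, 10 = I gained maximum knowledge".

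Table 1 (under Process evaluation) has one row for "Subjective knowledge", marked at T0 and T1 only.

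The Statistical analysis section then states: "On data from questionnaires filled out on more than one occasion (e.g. empowerment, coping strategy, knowledge) we will use a repeated measurement analysis". The purpose given for that analysis is "to test if both research groups diverged from baseline to follow-up". Single-occasion outcomes are handled separately: "With data that will be measured on one occasion (e.g. claimant satisfaction, insurance physicians satisfaction and perceived justice) we will use t-tests". Knowledge is not among the examples given there.

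**The concern.** A repeated-measures test of divergence from baseline needs the same quantity on each occasion. Here the first score is a level and the second is a perceived change. The document treats the two as one outcome measured twice, and no quantity is in fact measured twice.

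The stake is a secondary outcome that the authors care about. The Abstract lists knowledge among the secondary outcomes. Raising it is the first objective in Step 2 of the intervention's development, and the Discussion uses it to link empowerment with claimants' expectations and, through those, with perceived justice. If the analysis is run and reported as written, readers would be shown a course of knowledge over time that the data cannot supply. Depending on the model, the arm comparison may also lose precision for no benefit.

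**Working it through.** The plan gives no figure for this outcome, so there is none to reproduce. The check has three steps.

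**1. What the difference score means**

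| | T0 | T1 |
|---|---|---|
| Quantity | how much is known | how much was gained |
| Score 1 | no knowledge | no gain |
| Score 10 | complete knowledge | maximum gain |

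T1 minus T0 is (perceived gain) minus (baseline level). A claimant who rates 8 at T0 and learns nothing rates 1 at T1, and 1 - 8 = -7, although knowledge did not fall. One who rates 8 and learns a little (T1 = 3) gets 3 - 8 = -5, although knowledge rose.

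The same happens to means. With an assumed T0 mean of 5 and assumed T1 gain means of 3 (control) and 4 (intervention), the average change is 3.5 - 5 = -1.5. That looks like a loss, although both arms report a gain.

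**2. What the group-by-time contrast estimates**

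Randomization follows the baseline questionnaire, so the T0 means are equal in expectation. With the same assumed means, (4 - 5) - (3 - 5) = 1 and the T1 difference alone is 4 - 3 = 1. The contrast is the arm difference in perceived gain. It is not biased by T0, but it is not a difference in change of knowledge level either.

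**3. Precision**

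Inputs:
- 86 per arm is the Sample size section's figure for empowerment, borrowed here, with its two-sided reading of alpha = 0.05.
- The 0.5 SD arm difference in the T1 item, equal SDs at T0 and T1, and the T0–T1 correlation r are assumptions that are not in the document.

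Formulas, relative to the variance s² of the T1 score:
- T1 alone: factor 1
- Unadjusted change: Var(T1 - T0) = s²(2 - 2r), factor 2 - 2r
- T1 with T0 as covariate: factor 1 - r²

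The noncentrality for T1 alone is 0.5 × √(86/2) = 3.28. For the other analyses, divide by the square root of the factor. By the normal approximation, power is Φ(noncentrality - 1.96).

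| r | Change: factor | Noncentrality | Power | Covariate: factor | Noncentrality | Power |
|---|---|---|---|---|---|---|
| -0.3 | 2.6 | 2.03 | 0.53 | 0.91 | 3.44 | 0.93 |
| 0 | 2.0 | 2.32 | 0.64 | 1.00 | 3.28 | 0.91 |
| +0.2 | 1.6 | 2.59 | about 0.73 | 0.96 | 3.35 | 0.92 |

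T1 alone has power of about 0.90 (0.906 by the normal approximation, 0.903 by the t distribution). A simulation of the same setting (T1 means 3 and 4, SD 2, so 0.5 SD) agreed. Over r from -0.6 to +0.2, the standard error was 0.39 to 0.55 for the change score against 0.30 for T1 alone, and power was 0.44 to 0.72 against 0.90.

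**The case against.** The case for leaving the plan alone has several parts.

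- **The arm comparison is unbiased.** The section speaks of the groups diverging, which is a between-arm question, and randomization balances T0 in expectation. This stands. A reader might infer that the treatment effect on knowledge is biased; the design does not support that. What remains is a wrong label, time and within-arm terms without meaning, and possibly lost precision.
- **The model is not specified.** A longitudinal model with baseline as covariate also fits the plan's words, and it loses no power. This stands too, so the loss is conditional on an unadjusted change analysis. The choice of model does not cure the mismatch, because no model turns a gain rating into a second level rating.
- **The power figures rest on assumptions.** The effect size, the SDs and the correlation are all assumed, and nothing in the document says whether r is negative or positive. The 86 per arm is what remains after 25% dropout allowed for empowerment, and more may remain at T1, about two weeks after baseline. It would be tempting to quote 53% as this trial's power for knowledge; the document does not support that.
- **Control-arm wording.** One might infer that the T1 question is leading or meaningless for controls, since it refers to the intervention. Both arms receive a website and claimants are blinded to the design, so a control may take the phrase to mean the site provided. The questionnaires are in Additional file 2, which is not shown, so the wording put to controls cannot be checked. This is a matter to clarify and is not an established fault.
- **It is one secondary item.** This is true. The primary outcome and the sample size rest on empowerment, and no mediation analysis through knowledge is described.

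**Conclusion.** The inconsistency is real and can be read directly from the document: a level at T0, a perceived gain at T1, no second level rating, and a planned test of divergence from baseline. For this outcome the named analysis cannot answer the question set for it. Time effects and within-arm changes in knowledge should not be interpreted at all. The between-arm contrast remains valid as a comparison of perceived gain.

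The cost in precision ranges from none, if T0 enters as a covariate, to a fall in power from about 0.90 to roughly 0.53–0.73 with an unadjusted change score. That range rests on the assumed 0.5 SD effect, 86 per arm, equal SDs and correlations from -0.3 to +0.2.

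This is a correction to a secondary outcome. A reader might take it as a threat to the trial's main conclusion; it is not, because the empowerment analysis and its sample size are untouched.

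**What to change.** 1. In the Statistical analysis section, remove knowledge from the repeated-measures examples. Compare the T1 gain rating between arms as a one-occasion outcome, adjusted for the T0 level, and report it as perceived gain in knowledge. This costs one sentence, needs no new data and covers every participant.
2. For claimants who have not yet reached T1, where feasible, also ask the T0 question word for word at T1, and analyse that rating by ANCOVA on the T0 rating. This costs one online item. Data collection began in January 2009, so it changes a questionnaire already in use in an ethics-approved trial and gives the level outcome only for later participants. It should therefore supplement item 1, and the number of participants contributing should be reported.

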#### Claimants expectation

Questions concerning expectations of claimants on the outcomes of their disability assessment will be asked at T_0_, T_1 _en T_2_. Subjects will be asked whether they expect to receive a disability benefit after the disability assessment (yes/partly/no) and the reason for this belief.

#### Coping strategy

To evaluate if the intervention also might lead to a different coping strategy within claimants, we will measure coping strategy with the Dutch adaptation of the Ways of Coping Questionnaire (WCQ, [52]). This questionnaire is based on Lazarus' Theory of Stress and Coping [53], which states that coping is situation-specific rather than a trait or disposition. Three dimensions of the WCQ are included: Problem Solving (8 items), Seeking Social Support (6 items) and Avoidance (7 items). Questions from these scales are adapted to the context of the disability assessment.

#### Perceived Work Ability

Perceived work ability will be assessed with the first item from the Work Ability Index (WAI) [54]. This question asks subjects to rate their current work ability compared to their lifetime best on a 10-point scale, ranging from *completely unable to work *(score '0') to *work ability at its best *(score '10').

### Other variables

#### Socio-demographic

At baseline, socio-demographic data (gender, age, level of education, current work status, working hours per week, nationality, Internet use and disability type) will be collected.

#### Claimants preparation

Claimants from the intervention group and control group will be asked about their preparation for their disability assessment at the T_1 _measurement. Questions such as "How much time did you spend on gathering information about disability assessment procedures" or "Which websites did you visit to obtain information about the WIA benefit" will be asked.

Additionally, use of the website intervention (e.g. amount of mouse-clicks on the website, total login time, use of particular components) will be collected up to four months after the disability assessment.

#### Return to work (RTW)

With data from UWV we will determine claimants working status four months after disability assessment. Return to work data will be categorized into full, partial or no return to work.

After finishing the study's inclusion period, we will obtain data from UWV on claimants' official objections and appeal.

### Process evaluation

Among the participants of the intervention group, experiences with the use of the intervention will be evaluated. This evaluation will be assessed with a brief questionnaire at T_3_. This questionnaire contains both quantitative (e.g. a generic grade for the website) and qualitative questions (e.g. "Do you have any suggestions to improve the website?"). Reasons for complying or not complying will be asked in this questionnaire as well, in order to obtain insight into the potential success of implementation.

Furthermore, the website http://www.wiagesprek.nl will automatically collect data on website usage, so that we can determine compliance and which components are most frequently used. All actions on the website of each claimant will be tracked and stored in a database.

After finishing the research, we will interview five claimants and five insurance physicians, who assessed disability of study participants, on their experiences with the intervention.

For an overview of measurements, see table 1.

**Table 1 T1:** Schedule of measurements

Outcome measure	T_0_: 2 weeks prior to disability assessment	T_1_: Prior to disability assessment	T_2_: After disability assessment	T_3_: 6 weeks after disability assessment	T_4_: 4 months after disability assessment
*Empowerment**	X	X			X

*Claimants satisfaction*			X		

*Perceived Justice*				X	

*Subjective knowledge*	X	X			

*Claimants expectations*	X	X	X		

*Coping Strategy*	X	X			

*Perceived Work Ability*	X	X			X

*Claimants preparation*		X			

*Return to Work*					X

*Process Evaluation*				X	

*Physicians satisfaction*			X		

* The following subscales from the VrijBaan empowerment questionnaire are included in the questionnaire:

T_0_: all subscales

T_1_: subscale Competence and Impact

T_4_: all subscales

NB: The Pearlin Mastery Scale and the General Self-efficacy scale can be distracted from the T_0_, T_1 _and T_4 _measurement

### Statistical analysis

Baseline values will be analyzed for differences between the two groups, by one-way-analysis of variance for numerical data and chi-square for categorical data. The primary analysis will be a comparison of the change in empowerment between the intervention and control group following the "intention-to-treat" principle. On data from questionnaires filled out on more than one occasion (e.g. empowerment, coping strategy, knowledge) we will use a repeated measurement analysis to test if both research groups diverged from baseline to follow-up. With data that will be measured on one occasion (e.g. claimant satisfaction, insurance physicians satisfaction and perceived justice) we will use t-tests to detect possible differences between the two research groups. Additionally, a per-protocol analysis will be performed.

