### Sample size

A power analysis has been carried out for the main outcome measure, i.e. empowerment. Empowerment will be measured using the "VrijBaan" questionnaire [43]. This questionnaire consists of six subscales. Based on previous findings the expected standard deviation (SD) for each of these scales is 0.70 [43]. Power calculations indicate that, to detect a 10% difference in empowerment, 86 subjects are necessary in each study group (assuming that power = 0.90 and α = 0.05). Taking into account a drop out rate of 25%, a sample size of approximately 230 claimants will be required.

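### The primary analysis compares change from baseline without adjusting for T0, while the sample size uses a raw-score SD; adjusting for T0 would be more precise at no cost

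*Protocol article*

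**What the plan says.** The Statistical analysis section defines the primary analysis: "The primary analysis will be a comparison of the change in empowerment between the intervention and control group", by intention to treat. For outcomes measured more than once, with empowerment given as an example, it adds: "we will use a repeated measurement analysis to test if both research groups diverged from baseline to follow-up". It does not mention the T0 score as a covariate.

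The Sample size section rests on a different quantity: "Based on previous findings the expected standard deviation (SD) for each of these scales is 0.70". From this it derives that "to detect a 10% difference in empowerment, 86 subjects are necessary in each study group", "assuming that power = 0.90 and α = 0.05", and then: "Taking into account a drop out rate of 25%, a sample size of approximately 230 claimants will be required". It gives neither an SD of change nor a correlation between baseline and follow-up.

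Table 1 and the Primary outcome section fix the visits. All six VrijBaan subscales are measured at T0 and T4; only Competence and Impact are also measured at T1. According to the Randomization section, T0 is completed before allocation.

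**The concern.** The quantity that is tested and the quantity used for sizing are not the same. An SD of 0.70 describes the spread of a score at one visit. The spread of a change from T0 depends on how strongly the two visits are correlated, and it can be smaller or larger than 0.70.

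Two things are at stake:

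- **Meaning of the stated power.** The figure of 0.90 carries over to the stated analysis only under a condition on the correlation that the article does not mention. T0 to T4 spans about 18 weeks (2 weeks before the assessment, 16 weeks after it) and includes both the assessment and the benefit decision. A high correlation should therefore not be taken for granted.
- **Precision given away.** The T0 score is already collected before randomization. Used as a covariate, it gives a more precise estimate of the arm difference than subtracting it does, whatever the correlation.

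**Working it through.** **Inputs.** From the Sample size section: SD 0.70, power 0.90, α 0.05, 86 per group, dropout 25%, total about 230. Assumptions: the test is two-sided (the article does not say), the SDs at T0 and T4 are equal, and r is shown over a range because it is not given.

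**Step 1: reproduce the plan's figures.** The 10% difference is not given in points, so it has to be inferred. Solving for the difference detectable with 86 per group:

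0.70 × √(2/86) × (1.960 + 1.282) ≈ 0.346, or about 0.35 points.

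Taking 0.35, the normal approximation gives 85 per group and the exact t calculation gives 86 (power 0.903). A one-sided test would need only 69 by the normal approximation, so two-sided is the reading that fits. For dropout, 86/0.75 = 114.7, rounded up to 115 per group, or 230 in total. The stated figures are thus reproduced as a two-sample comparison of raw scores with SD 0.70.

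**Step 2: variance of the stated analysis.** With two visits, a group-by-time test that treats T0 as an outcome is the same as a t-test on change. Per claimant:

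- change score: 2(1−r)SD²
- ANCOVA on T0: (1−r²)SD²
- ratio, change to ANCOVA: 2(1−r)/[(1−r)(1+r)] = 2/(1+r)

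The ratio exceeds 1 at any r below 1. It is 1.54 at r = 0.3, 1.33 at r = 0.5 and 1.18 at r = 0.7.

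**Step 3: when 0.70 is large enough for a change score.** The condition 0.70 × √(2(1−r)) ≤ 0.70 requires r ≥ 0.5. This threshold compares only the two SDs, so it does not depend on what 10% means in points.

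**Step 4: power at 86 per group and n per group for 90% power** (difference 0.35, exact t):

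| r | SD of change | Power, change | Power, ANCOVA | n, change | n, ANCOVA |
|---|---|---|---|---|---|
| 0 | 0.990 | 0.635 | 0.903 | 170 | 86 |
| 0.3 | 0.828 | 0.787 | 0.928 | 119 | 78 |
| 0.4 | 0.767 | 0.845 | 0.945 | 102 | 72 |
| 0.5 | 0.700 | 0.903 | 0.964 | 86 | 65 |
| 0.6 | 0.626 | 0.954 | 0.983 | 69 | 55 |
| 0.7 | 0.542 | 0.988 | 0.995 | 52 | 44 |

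**Step 5: unequal SDs.** Measured against a follow-up SD of SD₁, the threshold becomes r ≥ SD₀/(2·SD₁). With SD₀ = 0.70 it is 0.44 if SD₁ = 0.80 and 0.58 if SD₁ = 0.60. The ordering of the two methods does not reverse: the variance of change minus the ANCOVA variance is (SD₀ − r·SD₁)², which is never negative.

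**The case against.** The strongest reply is that no shortfall has been demonstrated. A change comparison is valid and unbiased under randomization. If r is 0.5 or more, the stated 0.90 is met, and at r = 0.7 the two methods differ by less than one percentage point of power. Nothing in the article points to r below 0.5. This stands. A reader might infer that the trial is underpowered, but the documents do not support that, because they give no correlation.

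Second, the two-visit formula does not cover everything. Competence and Impact have three visits. If the contrast is the mean of T1 and T4 minus T0, with equal correlations, its variance is (1+r)/2 + 1 − 2r = 1.5(1−r) in units of SD². The threshold then falls to r = 1/3, and power at r = 0.3 is about 0.89. This also stands, so the 0.5 threshold belongs to the T0–T4 comparison. It is the only comparison available for the other four subscales.

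Third, a repeated measurement analysis could be a model that constrains the arms to a common baseline mean, which recovers about the precision of ANCOVA. That is possible, but the text specifies no such model. What it does state is a comparison of change.

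Three further criticisms might be drawn from the same section, but they do not support this point:

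- **Incomplete visits.** Loss of claimants who miss a visit would follow from a classical repeated-measures ANOVA, which the article does not name. Four subscales have no T1 value to miss.
- **Baseline tests.** The planned significance tests of baseline differences are uninformative, but no later step uses their result.
- **Dropout inflation.** Enlarging the sample for 25% dropout so that completers reach the target is ordinary practice.

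**Conclusion.** The point holds as a free improvement. The article commits to a comparison of change and sizes it with a raw-score SD. For the T0–T4 comparison with equal SDs, this is less precise than adjustment for T0 at any r below 1, by a variance factor of 2/(1+r). The stated power applies to the change score only if r is at least 0.5, whereas with ANCOVA 86 per group gives about 0.90 or more at any r ≥ 0.

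The efficiency loss follows from the formulas. It is a large-sample result, and the one degree of freedom that the covariate costs is negligible at 86 per group. The power shortfall is conditional on r. Every power figure also rests on the inferred 0.35-point difference and a two-sided test.

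**What to change.** In the Statistical analysis section, replace the comparison of change with wording to this effect:

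- **Primary comparison.** For each VrijBaan subscale, the between-arm difference at T4 adjusted for that subscale's T0 score (ANCOVA), with 95% CI, including every randomised claimant with a follow-up value.
- **Competence and Impact**, which also have T1: a linear mixed model with T1 and T4 as outcomes and arm, visit, arm-by-visit and T0 score (by visit) as fixed effects.
- **Other repeated outcomes.** The same T0 adjustment for coping (follow-up at T1 only) and perceived work ability (T1 and T4). It should not be applied to subjective knowledge, where the T0 and T1 questions differ, or to claimants' expectation, which is categorical.

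The cost is analysis wording only. All the scores needed are already scheduled, and 86 per group stands without a correlation having to be assumed, because ANCOVA reaches 0.903 even at r = 0 under the inferred difference.
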